## Abstract

**Background:**

Various treatments are available for reducible unstable fractures of the distal radius, such as closed reduction combined with fixation by external fixator (EF), and rigid internal fixation using a locked volar plate (VP). Although there are studies comparing these methods, there is no conclusive evidence indicating which treatment is best. The hypothesis of this study is that surgical treatment with a VP is more effective than EF from the standpoint of functional outcome (patient-reported).

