Margaliot and collaborators [17], published a systematic review of treatments for distal radius fractures, in which 28 studies with 917 patients were analyzed. The authors concluded that the advantages of osteosynthesis by locked VP are not supported by the literature when compared with an external fixator, and that randomized clinical trials, as guidance for treating such patients, are lacking. A Cochrane Collaboration systematic review [19] of the literature on surgical procedures for the treatment of distal radius fractures analyzed 48 randomized studies comparing different methods of surgical treatment, and it was concluded that insufficient scientific information was available to determine which surgical treatment method was best for this type of fracture. Regarding complications, some studies report a considerable incidence of complications with the use of VP [16], while other studies indicate greater complications with the EF method [9].

David and collaborators [20] published a systematic review of treatment for distal radius fractures that analyzed 12 studies with 1,011 patients. The authors concluded that there are an insufficient number of randomized clinical trials comparing osteosynthesis using a locked VP versus external fixation for the treatment of distal radial fractures.

Therefore, we conceived this study based on the hypothesis that the use of locked volar plates in young patients with unstable distal radius fractures will provide better results in terms of patient-reported functional outcomes. It is also anticipated that there will be a shorter time for returning to work, better radiographic parameters, and a lower rate of complications when compared to the external fixation method at the end of a one-year follow-up period. The objectives of the study are to determine which is the most effective method for treatment of young patients with unstable fractures of the distal radius: rigid internal fixation with a locked volar plate versus an external fixator combined with PKW. The primary outcomes that will be evaluated is patient-reported function via the “Disabilities of the Arm, Shoulder and Hand” (DASH) questionnaire [21] and pain [“Visual Analog Pain Scale” (VAPS) [22] and digital algometer]. The secondary outcomes that will be evaluated are as follows: radiographic parameters, objective functional evaluation (goniometry and dynamometry), and rates of complications and failures (intention-to-treat principle).

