#### Primary outcomes

Patient-reported functional outcomes

Functional status will be evaluated by means of the DASH questionnaire (validated for the Portuguese language [28]) at the following intervals: 2 weeks PO, 8 weeks PO, 12 weeks PO, 6 months PO, and12 months PO.

Pain

Will be evaluated by means of the VAPS and an algometer [29,30] (the digital algometer used will be a FPIX 50 – Wagner Pain Test Digital Algometer), which is to be applied in the location where pain is reported by the patient, at the following times relative to treatment: 2 weeks PO, 8 weeks PO, 12 weeks PO, 6 months PO, and 12 months PO.

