### Statistical methods

Epidemiological data will be collected (age, sex, type of fracture, time between fracture, and treatment). Standard deviations or confidence intervals, in the case of percentages, will be provided for each type of data. As a method for confirming randomization effectiveness, data will be compared when stratified by assignment group.

The assumption of normality will be verified by the Shapiro-Wilk test for the use of parametric tests. A Pearson’s chi-square test will be employed to analyze results from the two groups involving categorical variables. A Student’s (parametric) *t*-test will be used for comparing groups of numeric variables. Paired t-tests (parametric) and Wilcoxon tests (non-parametric) will be used to compare clinical progression at intervals of 2-, 8-, and 12-weeks PO and subsequently at 6- and 12-months PO. The significance level used in all statistical tests is to be 5% (alpha = 0.05), with tests having a P value less than 0.05 being statistically significant.

Should differences be found in primary outcomes, then statistical methods will be used to test whether there is robust correlation between epidemiological factors or fracture seriousness and the observed functional outcomes. In addition, we intend to employ Kaplan-Meier survival analysis to evaluate drop-outs should high rates of complications (greater than 20%) occur in either assignment group.

Patients who experience treatment failures and require additional surgery will be monitored and their results computed in the primary assignment group (intention-to-treat principle). Provisions are to be made for blinded statistical analysis of data by a statistician who is unfamiliar with the objectives and outcomes of interest.

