### Sample size calculation

The sample size was calculated based on a 10 point difference (10%) in the DASH between the two groups studied, assuming a 95% confidence interval, 80% statistical power and 20% sampling error, resulting in 36 patients in each group.

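### Three primary measures at five visits, every test at 5% and no primary visit named: the error rate of the primary claim is not held at 5%

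*Protocol article*

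**What the plan says.** - **Primary measures.** Under Primary outcomes the article places function ("Functional status will be evaluated by means of the DASH questionnaire") and pain ("Will be evaluated by means of the VAPS and an algometer"). The Abstract and the objectives at the end of Background give the same set, the latter beginning "The primary outcomes that will be evaluated is patient-reported function" and going on to pain by VAPS and algometer.
- **Visits.** Primary outcomes and Table 2 schedule all three measures at 2 weeks, 8 weeks, 12 weeks (3 months), 6 months and 12 months. No visit is marked as the primary one.
- **Testing rule.** Statistical methods assigns Student's t-test to between-group comparison of numeric variables without naming a visit. It states "The significance level used in all statistical tests is to be 5% (alpha = 0.05" and applies the same threshold to declare any single result significant. Further analyses are triggered if differences appear in the primary outcomes (plural), with no order among them and no statement of whether one or all must differ.
- **Priority of DASH.** The Abstract hypothesis is that "surgical treatment with a VP is more effective than EF from the standpoint of functional outcome (patient-reported". Sample size calculation rests on a 10-point DASH difference, "assuming a 95% confidence interval, 80% statistical power and 20% sampling error", giving 36 per group. Neither place names a visit, and no sample-size basis is given for pain.
- **Blinding.** Clinical outcomes states that evaluators are blinded to allocation for the 6- and 12-month outcomes.

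**The concern.** A 5% level protects one pre-specified comparison. Here the text allows up to fifteen between-arm comparisons to carry the label primary, each judged at 5%, and does not say which of them decides the trial. A significant result on any measure at any visit could be reported as a primary finding while following the plan to the letter.

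The choice of visit is not neutral. Background describes external fixation as needing longer immobilisation and longer functional recovery, so an early visit and the one-year visit may answer different questions. The early visits are also those without stated evaluator blinding, and DASH and VAPS are reported by patients.

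**Working it through.** **1. The plan's own figure.** For two means, n per group = 2·SD²·(1.960 + 0.842)²/Δ². No SD is stated, so 36 cannot be confirmed or refuted. Solving for the SD with Δ = 10 and n = 36 gives SD = (10/2.802)·√18 ≈ 15.1 (two-sided 5%, 80% power, no attrition). If the 20% sampling error means attrition, the implied SD is about 13.5-13.8. Either way, 36 per group is the size for one DASH test at 5%.

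**2. Number of possible primary comparisons.** 3 measures × 5 visits = 15. Visits without stated evaluator blinding: 2 weeks, 8 weeks and 3 months, so 3 × 3 = 9 of 15.

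**3. Independent tests, no true difference.** The chance of at least one P < 0.05 among k tests is 1 − 0.95^k. In one given direction it is 1 − 0.975^k, because each two-sided 5% test puts 2.5% in each tail.

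| Family | k | Either direction | Favouring volar plate |
|---|---|---|---|
| Three measures, one visit | 3 | 14.3% | 7.3% |
| DASH, five visits | 5 | 22.6% | 11.9% |
| Three measures, five visits | 15 | 53.7% | 31.6% |

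**4. Correlated tests.** Repeated measures on the same patients are correlated. The article gives no correlations, so these are assumptions. Simulation of multivariate-normal z statistics (200,000 draws, the same correlation between any two visits, and between-measure and between-visit correlations multiplied):

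| Between measures | Between visits | 15 tests, either direction | 15 tests, favouring volar plate |
|---|---|---|---|
| 0.3 | 0.5 | 44% | 23% |
| 0.5 | 0.5 | 41% | 21% |
| 0.5 | 0.7 | 34% | 17% |
| 0.7 | 0.8 | 26% | 13% |

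A check with actual t-tests at 36 per group (correlations 0.3 and 0.5) gave 44.5%. If correlation decays with the distance between visits (AR(1)), the either-direction figures over the same range are slightly higher, about 30-47%.

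**5. Smaller families, correlated.** DASH alone over five visits, with visit correlation 0.5, 0.7 and 0.8: 18%, 15% and 13% in either direction (9%, 7% and 6% favouring the volar plate). Three measures at one visit, with correlation 0.3 to 0.7: 14% to 11% in either direction. So treating DASH as the implicit main outcome does not restore 5% unless a visit is fixed, and fixing a visit does not restore it while three primaries remain.

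**6. Cost of the alternatives at SD 15.14.** One DASH test at 0.05: power 80% with 36 per group. Bonferroni over three measures at one visit (0.05/3 = 0.0167): DASH power 66%, or 48 per group for 80%. Bonferroni over 15 tests (0.05/15 = 0.0033): power 45%, or 66 per group.

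**The case against.** - **The plan does not prescribe 15 tests.** The t-test sentence names no visits. The sentence that lists visits concerns paired and Wilcoxon tests of progression, which are within-patient. No rule says that one significant result makes the trial positive, and if all primaries had to be significant, error would not inflate. This stands: the 15-test figures describe what the wording permits.
- **A positive result is not shown to be likely.** A reader might infer from the 54% that a false-positive primary result is more likely than not. That needs independence or something close to it, which repeated measures on the same patients will not give. The figure also counts either direction, and the hypothesis is about the volar plate being better.
- **DASH is singled out to a degree.** A reader might infer that nothing in the plan points to a deciding comparison. The hypothesis and the sample size both point to DASH. What remains open is the visit and the standing of pain.
- **The statistician sentence.** The article has the data analysed blind "by a statistician who is unfamiliar with the objectives and outcomes of interest". A reader might infer that nobody analysing the data would know the primary comparison. The natural reading is an awkwardly worded masking safeguard, so it is not evidence here.
- **Early visits are not plainly one-sided.** Volar-plate patients wear a splint until postoperative day 14, and no fixator removal time is given. The direction of any early difference is therefore not established.
- **A separate analysis plan could handle multiplicity.** This is true of adjustment procedures in general. It is weaker here because the article itself fixes 5% for all tests and lists three primaries. An adjusted level elsewhere would contradict it.

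**Conclusion.** The point holds as a defect in what the protocol states. Three measures are primary, five visits are equal in standing, every test is at 5%, and no rule orders or combines them, so the error rate of a claim on a primary outcome can exceed 5%.

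If every measure is compared at every visit and any P < 0.05 counts, the risk is about 25-45% for assumed correlations of 0.3-0.7 between measures and 0.5-0.8 between visits, with 54% as the independent-test limit. In favour of the volar plate it is about 13-23% (32% if independent), against 2.5% for one two-sided test. With DASH alone over five visits it is about 13-18% in either direction. The exact size depends on the assumed correlations and on that reading of the plan. The documents do not support saying that a false-positive result is likely, or that DASH has no priority.

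The one-year phrase in Background does not settle the visit, because its sentence concerns return to work, radiographs and complications. The 12 months in Clinical outcomes is a minimum follow-up. The matter should be settled before any unblinded data are seen, because it determines what counts as success.

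**What to change.** State in Primary outcomes and Statistical methods: *The single primary outcome is the between-arm difference in DASH at 12 months, tested two-sided at 0.05. VAPS, algometer and DASH at all other visits are secondary and are reported with 95% confidence intervals.* Align the Abstract and the objectives.

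This follows the hypothesis and the sample-size basis, uses the last scheduled visit, and places the deciding comparison at a visit with stated evaluator blinding. The basis for 36 per group is unchanged.

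The cost is that pain can no longer be claimed as a primary result, and the registry and ethics records need a matching amendment. If the sponsor wishes to keep several primaries, a stated multiplicity procedure with a rechecked sample size would also close the gap, at the price in power or patients shown in the working.

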**Methods/Design:**

The study is randomized clinical trial with parallel groups and a blinded evaluator and involves the surgical interventions EF and VP. Patients will be randomly assigned (assignment ratio 1:1) using sealed opaque envelopes. This trial will include consecutive adult patients with an acute (up to 15 days) displaced, unstable fracture of the distal end of the radius of type A2, A3, C1, C2 or C3 by the Arbeitsgemeinschaft für Osteosynthesefragen–Association for the Study of Internal Fixation classification and type II or type III by the IDEAL^32^ classification, without previous surgical treatments of the wrist. The surgical intervention assigned will be performed by three surgical specialists familiar with the techniques described. Evaluations will be performed at 2, and 8 weeks, 3, 6 and 12 months, with the primary outcomes being measured by the Disabilities of the Arm, Shoulder and Hand (DASH) questionnaire and measurement of pain (Visual Analog Pain Scale and digital algometer). Secondary outcomes will include radiographic parameters, objective functional evaluation (goniometry and dynamometry), and the rate of complications and method failure according to the intention-to-treat principle. Final postoperative evaluations (6 and 12 months) will be performed by independent blinded evaluators. For the Student’s *t*-test, a difference of 10 points in the DASH score, with a 95% confidence interval, a statistical power of 80%, and 20% sampling error results in 36 patients per group.

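### DASH is compared by an unadjusted t-test, and the prognostic factors collected are used only after a positive result, so precision is given up in a trial of 36 per arm

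*Protocol article*

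**What the plan says.** All of this is in the protocol article under Statistical methods, unless another section is named.

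- **Data collected:** "Epidemiological data will be collected (age, sex, type of fracture, time between fracture, and treatment". I read the last two items as one variable, the time from fracture to treatment.
- **Baseline comparison:** "As a method for confirming randomization effectiveness, data will be compared when stratified by assignment group".
- **Treatment comparison:** a Student's t-test between groups for numeric variables, with no covariates. The Abstract builds the sample size on the same test.
- **Use of the prognostic factors:** "Should differences be found in primary outcomes, then statistical methods will be used to test whether there is robust correlation between epidemiological factors" or fracture severity and the functional outcomes. The methods for this step are not named.
- **Allocation:** the Abstract says "Patients will be randomly assigned (assignment ratio 1:1) using sealed opaque envelopes". Randomization and Masking describes a software-generated sequence in consecutively numbered envelopes and mentions no stratification.

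**The concern.** The eligible fractures run from AO types A2 and A3 to C1, C2 and C3, and cover IDEAL types II and III. The IDEAL score itself counts age, energy and associated lesions, so the authors already treat such features as relevant to severity. If these factors predict DASH, their contribution stays in the error term of the t-test and widens the confidence interval for the treatment difference. With 36 per arm and no stratification described, chance differences in case mix between the arms are also plausible.

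The trigger for using the factors is poorly aimed. After a positive result they are examined. After a null result, when residual variance or an unlucky split could have hidden an effect, the article provides no further look. The prognostic analysis is therefore selected on the outcome. At stake is the chance of detecting the difference for which the trial was sized, and the standing of whatever the conditional analysis reports.

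**Working it through.** **Inputs from the document**
- Target difference: "The sample size was calculated based on a 10 point difference (10%) in the DASH between the two groups studied".
- Power and size: "assuming a 95% confidence interval, 80% statistical power and 20% sampling error, resulting in 36 patients in each group".
- Level: "The significance level used in all statistical tests is to be 5% (alpha = 0.05"), taken as two-sided because the sidedness is not stated.

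**Inputs assumed**
- SD of DASH: not stated, so back-solved below and varied from 13.8 to 20.
- R², the share of DASH variance explained by the covariates: not stated, so varied from 0.05 to 0.30.

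**Step 1: the plan's own figure.** The normal formula is n per group = 2·SD²·(1.960 + 0.842)² / 10². With SD 15 this gives 2 × 225 × 7.849 / 100 = 35.3, rounded up to 36. Solving for the SD at n = 36 gives 10 / 2.802 × √(36/2) = 15.1. The stated 36 therefore fits an SD of about 15 with no allowance for loss. It also fits an SD of 13.8 if 30 per group was multiplied by 1.2. The document does not settle which, so 36 cannot be reproduced from its own inputs alone.

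**Step 2: power of the planned t-test.** SE = SD × √(2/36). At SD 15, SE = 3.54, the noncentrality is 10 / 3.54 = 2.83 and the critical t on 70 df is 1.994. Power is 79.7%.

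**Step 3: power with adjustment.** Replace SD by SD × √(1 − R²). At SD 15 and R² = 0.20 the residual SD is 15 × √0.80 = 13.42, SE = 3.16, noncentrality = 3.16 and power is 88%. Power at 36 per arm (noncentral t):

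| Assumed SD | R² = 0 | 0.05 | 0.10 | 0.20 | 0.30 |
|---|---|---|---|---|---|
| 13.8 | 86% | 88% | 89% | 92% | 95% |
| 15 | 80% | 82% | 84% | 88% | 92% |
| 20 | 55% | 57% | 60% | 65% | 71% |

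Spending four degrees of freedom on covariates lowers these by less than 0.1 percentage point. In precision terms, 36 adjusted patients per arm do the work of 36 / (1 − R²) unadjusted ones: 40 at R² = 0.10 and 45 at R² = 0.20. At SD 15 the half-width of the 95% confidence interval falls from 7.1 to 6.3 points at R² = 0.20.

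**Step 4: check by simulation.** I ran 10,000 trials per setting at SD 15 and 36 per arm, comparing the t-test with a model containing treatment and one covariate. With no true difference, rejection was 4.8% to 5.0% unadjusted and 4.8% to 5.2% adjusted. With a 10-point difference, power was 79% to 80% unadjusted, against 83.3%, 87.2% and 91.1% adjusted at R² = 0.10, 0.20 and 0.30. The gain is not bought with false positives.

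**The case against.** The strongest reply is that nothing here is an error. An unadjusted t-test is valid in a randomised trial, and the sample size was built on it. An adjusted model could also sit in an analysis plan or full protocol that is not shown. The validity point stands in full. The point about unseen documents stands in part: the article's silence does not forbid an adjusted analysis. But the article itself fixes an unadjusted comparison and a result-dependent use of the factors, and those two choices can be judged as written.

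Some stronger readings are tempting, but the text does not support them.

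- **A data-driven treatment estimate.** A reader might infer that the treatment effect is adjusted only after a positive result. The conditional step is a correlation of prognostic factors with function. It is not described as replacing or re-testing the comparison of plate with fixator, so only the prognostic analysis depends on the result.
- **False alarms at baseline.** If the four collected variables were independent and each tested at 5%, at least one would look imbalanced in 1 − 0.95⁴ = 18.5% of properly randomised trials. But the article does not say that the baseline comparison uses P values, and it attaches no decision to it. The fair criticism is narrower: comparing arms tells little about whether randomisation worked.
- **Power after 20% loss.** A reader might take the 20% sampling error as attrition and compute power at 29 per arm. The term is not explained and could equally mean the type II error, so I do not rely on that case.
- **Very wide case mix.** Fractures must be acute, displaced and reducible by closed means, and the Background speaks of young patients. The mix of fracture types is real, but it is bounded.

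**Conclusion.** The point holds as a recommended improvement, not as a flaw that invalidates the trial. The planned comparison is unbiased and keeps its 5% level, but it leaves unused the covariates that the trial already collects. The conditional rule for prognostic factors makes that secondary analysis depend on the result.

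The gain could be modest or substantial. At SD 15 it is about 2 percentage points of power if the covariates explain 5% of DASH variance, and about 12 if they explain 30%. At SD 20 the corresponding gains are about 2 and 16 points, from a much lower start. SD and R² are both assumptions, and the document supports no particular R². That adjustment is worth prespecifying does not depend on the exact value, because the cost is negligible if R² turns out small.

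**What to change.** Under Statistical methods:

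1. Prespecify one covariate-adjusted comparison of DASH: treatment plus a short fixed list such as age, sex, fracture type and time from fracture to surgery. Fit it whatever the unadjusted result. Fix the coding of fracture type before outcome data are seen, and keep it coarse enough for 72 patients.
2. Keep the unadjusted t-test as a sensitivity analysis. The sample size need not change.
3. Label the conditional correlation analysis exploratory.
4. Present baseline data by arm descriptively, and drop the statement that the comparison confirms randomisation.

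The cost is wording only. Every variable is already collected, and no extra patients or visits are needed.
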